### Secondary and exploratory endpoints

The effect of ketamine on indices of acute postoperative pain severity (opioid consumption measured as oral morphine equivalents, and NRS pain scores) on the first three postoperative days (or until hospital discharge) will be assessed. Quality of recovery in the two trial treatment arms will be compared using the QoR-15 on day 1 post-surgery.

Measures of wellbeing and psychological distress using the EQ-5D-3L and K-10 are collected in all patients prior to surgery and at 3 and 12 months post-surgery. The relationship of change from baseline to 3 and 12 months post-surgery in these variables will be examined with respect to trial treatment effect.

Patients who deny the presence of pain at follow-up are also asked if they have experienced ‘discomfort’ in the area of the index surgery in the previous week, followed by a similar pathway of questions. This pursues a secondary hypothesis that some patients may experience chronic symptoms which they may not identify as pain, particularly neuropathic symptoms, but which may adversely affect quality of life. The incidence of, and treatment effect on, this novel endpoint will be investigated as secondary trial outcomes in parallel to CPSP and reported separately.

### Database

A custom designed central electronic database has been constructed and maintained by a commercial provider (Research Path Pty Ltd, Melbourne, Victoria, Australia) for randomisation, drug inventory management, and data collection. Data entry onto the central electronic database at each participating site is done via a password-protected, online web-based portal to a secure server. The database has the facility for transmitting data queries and requests for missing data, directly or via email notifications, to site research coordinators as well as data interrogation and cross-checking algorithms to minimise incorrect data entries and maximise data capture and completeness. Data completeness and outstanding data queries are continuously updated and displayed in the database portal for the attention of the trial management team to allow minimise missing data burden. The database will be held and maintained on a secure server after the trial completes with password-protected access available through agreement with the trial steering committee’s appointed data custodian.

### Data integrity and monitoring

In accordance with Good Clinical Practice (GCP) Monitoring guidelines, all participating sites undergo routine compliance monitoring, by way of centralised and on-site monitoring of randomly selected patient records, and may include a further telephone follow-up of a randomly selected sample of patients. Consent for this by patients is included in the Participant Information and Consent Form (PICF).

### Safety endpoints and adverse event reporting and monitoring

Data on a range of adverse events among recruited patients is recorded during admission, at discharge from hospital, and at 3 months post-surgery, with complications classified according to body system (cardiovascular, respiratory, neurological, gastrointestinal, urinary system, musculoskeletal, metabolic, and haematological) and including sepsis/infection, prolongation of hospital admission, need for re-operation, hospital readmission, and death. Classification of severity follows the NHMRC Guidance on safety monitoring and reporting in clinical trials involving therapeutic goods (November 2016) [28] and Common Terminology Criteria for Adverse Events (CTCAE) [31]. An adverse event (AE) is one where the nature and severity are consistent with the current Product Information Brochure. Serious adverse events (SAEs) and suspected unexpected serious adverse reactions (SUSARs) are reported for events that are unexpected given the participant’s underlying condition, and in the opinion of the investigator, the event is possibly related to the ROCKet trial solution infusion. SAEs and SUSARs are reported to the trial coordinating centre who are responsible for informing the relevant ethics committees and the administering institution for the trial, within 24 h of the site investigators becoming aware of the event, using a dedicated reporting form. These reports are reviewed by the DSMC.

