### Perioperative data collection

Preoperative data relevant to the risk of CPSP, including demographics, major co-morbidities, preoperative medications, and perioperative data, are collected. A baseline EQ-5D-3L [22] is collected in all patients for measurement of quality of life along with the Kessler K-10 Psychological Distress Scale [23], and in those who report preoperative pain in the area of the surgery, the modified Brief Pain Inventory short form (mBPI-sf) [24] and Neuropathic Pain Questionnaire (NPQ) [25] are completed.

Anaesthetic technique, medications, surgery type, time and date of surgery start and completion, and trial drug administration are documented. Time to discharge from the post-anaesthesia care unit (PACU) is recorded and quality of recovery is quantified using the QoR-15 [26] on postoperative day 1.

Acute postoperative pain severity is measured using opioid and other analgesic/antihyperalgesic drug consumption, and NRS pain scores, daily for the first 3 days or until discharge from hospital (whichever is sooner). Minimum, maximum, and mean NRS pain scores at rest and with movement or coughing are obtained each day from either the patient’s medical record or by direct questioning by trial research staff at least once daily. The Pain Catastrophising Scale (PCS), which measures catastrophic thinking related to pain [27], and the NPQ are completed on day 2 or earlier if discharged. The incidence and nature of side effects in hospital that are considered possibly related to the study drug by the treating clinicians are recorded daily. Where there was discontinuation of study drug infusion, this is recorded with the reason and time when this occurs.

The incidence of any of the trial safety endpoints are recorded. In line with National Health and Medical Research Council (NHMRC) guidelines, serious adverse events (SAE), serious adverse reactions (SAR), and suspected unexpected serious adverse reactions (SUSAR) are reported to relevant trial governance authorities and the data and safety monitoring committee (DSMC) [28].

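### The printed adverse-event definition and SAE reporting rule conflict with the article's own list of recorded events and with its other statement of what is reported

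*Protocol article*

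**What the plan says.** Three places in the Protocol article bear on this.

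*Safety endpoints and adverse event reporting and monitoring* (below, the safety section) begins with recording: "Data on a range of adverse events among recruited patients is recorded during admission, at discharge from hospital, and at 3 months post-surgery". The range covers complications by body system, "including sepsis/infection, prolongation of hospital admission, need for re-operation, hospital readmission, and death". No condition on cause or expectedness is attached. The section then defines its terms. For AEs: "An adverse event (AE) is one where the nature and severity are consistent with the current Product Information Brochure". SAEs and SUSARs share one rule, namely that they "are reported for events that are unexpected given the participant’s underlying condition, and in the opinion of the investigator, the event is possibly related"; the relation meant is with the trial infusion. Such reports go to the coordinating centre on a dedicated form, with a 24 h limit for onward notification, and "These reports are reviewed by the DSMC".

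*Perioperative data collection* gives a second reporting rule. Following NHMRC guidelines, "serious adverse events (SAE), serious adverse reactions (SAR), and suspected unexpected serious adverse reactions (SUSAR) are reported to relevant trial governance authorities" and to the DSMC. SARs are named as a category of their own, and no limit to unexpected or related events is stated.

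*Governance* gives the DSMC, which includes an independent statistician, the task of reviewing adverse-event and safety-endpoint data unblinded.

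**The concern.** Consistency with the product brochure is a test of whether a reaction is expected. It does not say what an adverse event is. Used as the definition, it shuts out most of the post-surgical events that the same section lists as adverse events.

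The SAE rule has a related fault. An SAE has to pass the same two judgements as a SUSAR, so the two labels select the same events. Both judgements are made case by case, and after major surgery many serious events can plausibly be put down to the operation or to the patient's disease. A reported SAE count by arm would then depend on attribution. A comparison of all serious events by arm protects against misattribution; a comparison limited to attributed events does not.

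Because the article gives a wider rule elsewhere, a reader of the final report could not tell which set of events an SAE count represents, and staff following one statement would report a different set from staff following the other.

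**Working it through.** No arithmetic decides this, and the article gives no figure to reproduce. The check is to set the statements side by side.

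**Step 1: the AE sentence against the opening list.** Read literally, an event that is not consistent with the brochure is not an AE. Re-operation, readmission and death after surgery are listed as recorded adverse events whatever their cause, and nothing suggests that they must match the brochure. A SUSAR, unexpected by its name, would also fall outside the definition.

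**Step 2: the SAE rule against the SUSAR rule.** One sentence covers both, with two conditions joined by *and*: unexpected for the patient's condition, and possibly related. The word unexpected and the suspicion of a drug reaction belong to the name SUSAR; neither belongs to the name SAE. With one shared test the categories merge. The SAR, named in *Perioperative data collection*, does not appear in the safety section.

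**Step 3: route four kinds of serious event through each rule.** The last column takes SAE in its ordinary sense (classed by seriousness), because *Perioperative data collection* prints no definition.

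| Serious event | SAE/SUSAR report under the safety section | Reported under *Perioperative data collection* |
|---|---|---|
| A. Judged unrelated to the infusion | No: fails the relatedness condition | Yes, as an SAE |
| B. Possibly related, but expected from the underlying condition | No: fails the expectedness condition | Yes, as an SAE and SAR |
| C. Possibly related, listed in the brochure, not expected from the condition | Meets the SAE/SUSAR test, but also fits the AE sentence: unclear | Yes, as an SAR |
| D. Possibly related, not in the brochure, not expected from the condition | Yes | Yes, as a SUSAR |

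The two sections disagree on A and B, agree on D, and leave C open. C is open because the two sentences use different yardsticks: the AE sentence refers to the brochure and the SAE/SUSAR sentence to the patient's condition.

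**Step 4: what catches A and B otherwise.** The opening list records deaths, re-operations, readmissions and prolonged stays at three time points without a filter. *Governance* gives the DSMC unblinded adverse-event data, and *Statistical analysis* provides an as-treated analysis of safety outcomes. The events are therefore captured. What changes between the two rules is whether they are classed as SAEs and enter the 24 h stream.

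**Step 5: scale, as illustration only.** *Statistical analysis* expects mortality of around 0.5% at 3 months. With the target of 4884 patients, 0.005 × 4884 = 24.4, so about 24 deaths. Each would be reported as an SAE under one section, and under the other only if judged both unexpected and possibly related. How many would fall on each side cannot be derived from the article.

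**The case against.** The strongest reply has three parts.

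First, this is a condensed article. *Trial status* names protocol version 5.0 as current, and that document may hold full definitions. Sites presumably work from it, so divergence between sites is conjecture. This stands in part: a missing SAR definition or seriousness criterion would be no finding, and actual divergence is not shown. It does not excuse the sentences that are printed. The article does not defer these definitions; it states them, and they disagree. Both sections refer to NHMRC guidance, but the safety section cites it for grading severity, which does not repair the AE sentence or the shared test.

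Second, restricting 24 h reports to possibly related events can be a deliberate and sensible choice where complications are common. That stands. The trouble is that the restriction is written as the rule for SAEs in general, and the other section does not carry it.

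Third, the safeguards in Step 4 of the working are real. This also stands, and it sets the limit of the point.

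Two stronger readings are tempting. A reader might infer that serious reactions listed in the brochure have no reporting route at all. The text does not support that: the SAE/SUSAR condition refers to the patient's condition, so a brochure-listed reaction that is possibly related and not explained by that condition meets it. A reader might also size the gap from the roughly 5% rate of psychomimetic effects quoted in *Background*. That rate covers all such effects, vivid dreams included, and says nothing about how many are serious.

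**Conclusion.** The point holds in a limited form. The AE definition is wrong as printed and conflicts with the section's own list. The SAE and SUSAR rules are merged. Serious events judged unrelated, or expected from the underlying condition, have no SAE/SUSAR report under the safety section but are reportable under *Perioperative data collection*. The status of brochure-listed serious reactions is unclear.

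The consequence is confined to how serious events are classified and which of them enter the 24 h stream. It would go too far to say that these events are lost or that the DSMC cannot see them. Deaths also enter the primary endpoint, because the primary estimand counts them as CPSP. Power, alpha and the primary analysis are unaffected, and the number of events concerned cannot be derived from the article.

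This rests on two assumptions: that SAE in *Perioperative data collection* has its ordinary meaning, and that adverse events in the DSMC's remit means the unfiltered recorded events and not the narrow definition printed in the safety section. The correction should be made because it bears on safety reporting and is cheap.

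**What to change.** 1. Reconcile the safety section with *Perioperative data collection* so that one rule states which events are reported, to whom and by when.
2. Define the terms separately: AE as any untoward event regardless of cause; SAE as an AE meeting a seriousness criterion; SAR as an SAE considered related; SUSAR as a related SAE that is also unexpected. Name a single reference for expectedness, which settles the brochure-listed case.
3. If a selective rule is intended, state that it governs expedited reporting only and does not define an SAE.
4. Tabulate all serious events by arm, regardless of attribution, for the DSMC and in the final report, using the complication data already recorded at the three time points.

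If protocol version 5.0 already contains consistent definitions, the first three items amount to correcting the article to match. The cost is a wording change and one routine table. No new data collection, sample-size change or change to the primary analysis is needed.

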### Sample size and study power

Trial sample size was initially calculated using CPSP incidence data at 12 months post-surgery, collected from a broad sample of patients who underwent major surgery and were recruited to the ENIGMA II trial and the ROCKet pilot study [6, 7, 16]. From this data, an incidence of CPSP at 12 months post-surgery of 12% was expected in the placebo arm. A 25% reduction in the incidence of CPSP by ketamine (i.e. a decrease from 12% to 9%, a risk ratio [RR] of 0.75) was hypothesised. Using a two-sided type I error of 4.9% (applying a correction for the pre-planned interim analysis of CPSP at 12 months at *n* = 1500 that allows stopping early for superiority using a conservative Haybittle-Peto boundary) and a power of 90%, recruitment of a total of 4396 patients was planned. Incorporating a 10% lost to follow-up rate at 12 months (similar to that encountered in the ENIGMA II follow-up study) [6], this leads to a final sample size of 4884 patients or 2442 per treatment arm.

Following alignment of the timing of the trial primary endpoint with the new ICD-11 definition of CPSP in 2022 [18, 19], the sample size was not changed. The observed pooled incidence (95% CI) of CPSP at 3 months post-surgery based on blinded EAC-adjudicated CPSP data from the first 1500 recruited patients included in the planned interim analysis is 24 (22–27)%. The observed loss to follow-up rate at 3 months post-surgery is approximately 6%. Assuming the final sample size of 4884 patients is achieved and using 22% as a conservative estimate of the overall incidence of CPSP at 3 months, the study has at least 80% power to detect a clinically significant reduction of at least 15% in incidence of CPSP at 3 months by ketamine (a decrease from 23.75% to 20.25%, or RR of 0.85).

### Statistical analysis

A detailed statistical analysis plan will be developed prior to unblinding of the data collected up to 3 months after surgery. In what follows, the analysis plan using data up to and including the primary endpoint data is described. A separate plan will be written before unblinding for the data collected up to 12 months post-surgery.

The analysis will include all randomised patients, excluding patients who had their surgery cancelled post-randomisation and did not return later for their planned surgery. For the analysis of the efficacy outcomes, patients will be reported and analysed according to their randomised study arm (i.e. ‘as randomised’). For the analysis of safety outcomes, patient data will be reported and analysed according to the intervention received (i.e. ‘as treated’), whereby those who did not receive at least one study treatment will be excluded from the analysis.

The primary estimand for the ROCKet trial is defined according to the addendum to the ICH E9 on estimands and sensitivity analysis in clinical trials [32]. The trial aims to answer the specific research question: does IV ketamine, given immediately prior to and for up to 72 h following surgical incision, compared to placebo, reduce CPSP at 3 months after surgery, measured by the relative difference in the incidence/risk (i.e. RR) of CPSP at 3 months after surgery between treatment arms, regardless of the post-randomisation (intercurrent) events listed below, while assigning the patients who died to have CPSP at 3 months?

Primary estimand attributes are:Treatment: IV ketamine, given immediately prior to and for up to 72 h following surgical incision, compared to placebo, allocation by randomisationPopulation: consenting adult patients presenting for elective or expedited surgery under anaesthesia for a variety of major surgeries associated with CPSPVariable: CPSP at 3 months post-surgeryIntercurrent events: not receiving trial solution during surgery will be handled using a treatment policy strategy, while death (expected incidence to be around 0.5% at 3 months) will be handled using a composite strategy by assigning the patients who died to have CPSP at 3 monthsPopulation level summary: relative difference in the incidence/risk (i.e. RR) of CPSP at 3 months after surgery between treatment arms (IV ketamine versus placebo)

The primary outcome of CPSP (yes/no) at 3 months after surgery will be analysed using a binomial log-linear regression model, with the placebo group as the reference, and in the model site, presence or absence of preoperative pain in the area of the surgery (stratification factors), and treatment. The primary hypothesis will be evaluated by obtaining the estimate of the RR for treatment and a 95.1% confidence interval (two-sided *α* = 0.049).

Binary secondary effectiveness outcomes will be analysed similar to the primary outcome and targeting a similar primary estimand, and for continuous secondary effectiveness outcomes, a linear regression model will be fitted with a model specification similar to that of the primary outcome. Sensitivity analysis will be conducted adjusting the model for pre-specified baseline covariates. Supplementary analysis targeting a different estimand with a different strategy for handling the intercurrent event of death will also be performed.

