## Background

Chronic post-surgical pain (CPSP) is recognised as one of the most common and debilitating complications of major surgery [1]. A number of surgical and psychosocial factors are associated with an increased likelihood of developing CPSP including severity of early (acute) postoperative pain, increased duration of surgery, open (as opposed to laparoscopic) surgical approach, intraoperative nerve damage, preoperative anxiety and fear, introversion, previous persistent pain, and mental health conditions [2–4].

Investigators studying the epidemiology of CPSP have highlighted that ‘an alarming proportion of patients…develop chronic postsurgical pain…’ and ‘… even the lowest incidences are unacceptably high’ [2, 3]. A review of CPSP found ‘one-year incidence to be highly variable and surgery specific, ranging from a low of approximately 10–15% following modified radical mastectomy…to a high of 61–70% for thoracotomy…and amputation’ [3]. These data are disturbing but are confirmed by a Norwegian national epidemiological study, which found an incidence of 40% at least 3 months post-surgery, and by prospective follow-up data from the large international ENIGMA (Evaluation of Nitrous oxide In the Gas Mixture in Anaesthesia) and ENIGMA II trials, which found an overall incidence of CPSP of 11–12% at 1 to 4 years after a broad range of major surgery [5–7]. There is relatively little data on the natural history of CPSP, and it is likely that the variation in incidence reported by studies reflects heterogeneity in surgical type and the methodology and timing of data collection which typically ranges between 3 months and 1 year post-surgery. A taskforce of the International Association for the Study of Pain (IASP) has recommended that chronic pain be defined as pain persisting for at least 3 months, as part of a new World Health Organisation (WHO) ICD-11 definition of chronic pain as a discrete disease state [8]. This definition has been extended to include CPSP and post-traumatic pain [9].

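### The primary model adjusts only for the stratification factors; bringing a short, named set of baseline predictors into it would add modest precision at little cost

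*Protocol article*

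**What the plan says.** In the protocol article, Statistical analysis, the binomial log-linear model for CPSP at 3 months has "in the model site, presence or absence of preoperative pain in the area of the surgery (stratification factors), and treatment". The primary hypothesis is judged on the RR from that model with a 95.1% confidence interval. Other covariates enter only afterwards: "Sensitivity analysis will be conducted adjusting the model for pre-specified baseline covariates". They are not named.

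Elsewhere the article describes predictors of CPSP:

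- Background cites a review that found "one-year incidence to be highly variable and surgery specific", from about 10–15% to 61–70%, and lists preoperative anxiety and mental health conditions among the risk factors.
- Subgroup analyses states that CPSP is commoner in younger patients, and uses surgical group (abdominal, thoracic/breast, orthopaedic, other), sex and age as subgroup factors.
- Perioperative data collection says that demographics and other preoperative data relevant to CPSP risk are recorded, with a baseline K-10 in all patients.
- Table 2 makes the planned type of surgery part of eligibility.

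Randomisation is stratified by hospital and preoperative pain only. On power, Sample size and study power says "the study has at least 80% power to detect a clinically significant reduction of at least 15" per cent, at an overall incidence of 22% that it describes as conservative.

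**The concern.** Adjusting a randomised comparison for baseline variables that predict the outcome narrows the confidence interval of the treatment effect without recruiting anyone. The article names such variables and collects them, but the primary estimate uses none beyond the two stratification factors. Any precision they offer goes to an analysis that does not decide the trial.

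This has some practical weight here. The power statement is conditional on reaching 4884 patients, and Progress and COVID-19 impact reports recruitment delays and a funding shortfall, since met by a further grant. The choice can be changed cleanly only until unblinding.

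**Working it through.** **Inputs from the article.** N = 4884, allocated 1:1; about 6% lost at 3 months; two-sided α = 0.049; 23.75% versus 20.25% (mean 22%); observed pooled incidence 24% (95% CI 22–27%).

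**1. The plan's own power.** Evaluable patients: 4884 × 0.94 ≈ 4591, so n ≈ 2295.5 per arm. For the two-proportion test with pooled variance under the null:

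power = Φ{[Δ − z√(2p̄(1−p̄)/n)] / √([p₀(1−p₀) + p₁(1−p₁)]/n)}

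with Δ = 0.035, p̄ = 0.22 and z = 1.9686.

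- Null standard error: √(0.3432/2295.5) = 0.012227
- Alternative standard error: √(0.34259/2295.5) = 0.012217
- (0.035 − 1.9686 × 0.012227)/0.012217 = 0.8946, so power = 0.8145

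The statement of at least 80% is reproduced, at 81.5%.

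**2. Power at the observed incidence.** With 24% overall and RR 0.85, the placebo rate is 0.24 × 2/1.85 = 25.95% and the ketamine rate is 22.05%. The same formula gives 86.9%.

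**3. Gain from added covariates.** If they explain a fraction R² of outcome variance beyond site and preoperative pain, the variance of the treatment effect falls by about a factor (1 − R²), which is equivalent to replacing n by n/(1 − R²). The article gives no R², so it is varied:

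| Assumed R² | Equivalent extra evaluable patients, 4591/(1 − R²) − 4591 | Power, 23.75% v 20.25% | Power, 24% overall, RR 0.85 |
|---|---|---|---|
| 0 | 0 | 81.5% | 86.9% |
| 1% | 46 | 81.8% | 87.2% |
| 2% | 94 | 82.2% | 87.5% |
| 5% | 242 | 83.4% | 88.5% |
| 10% | 510 | 85.3% | 90.1% |

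The first row is an unadjusted test. Adjustment for site and preoperative pain may already put the planned model a little above it.

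**4. What such R² values mean.** For a categorical predictor with shares w and incidences p around an overall m, R² = Σw(p − m)²/[m(1 − m)]. Assume three surgical groups with shares 40/20/40%:

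- incidences 15/25/27.5% give R² = 2.0%
- incidences 12/30/28% give R² = 3.9%
- incidences 10/40/25% give R² = 7.3%

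Expressed as a logistic risk score at 22% incidence, AUCs of about 0.60, 0.64 and 0.69 correspond to R² of about 2%, 4% and 9%. All of these are illustrations. They also ignore overlap with site and preoperative pain, which would lower them.

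**5. Chance imbalance in surgery type.** For a category holding an assumed one third of patients, the between-arm difference in share has SD √(2 × ⅓ × ⅔ / 2442) = 1.35 percentage points. With an assumed log-RR contrast of 0.80, a one-SD imbalance moves the log RR by 0.0135 × 0.80 ≈ 0.011. The standard error of the log RR at the planning rates is √[0.7625/(0.2375 × 2295.5) + 0.7975/(0.2025 × 2295.5)] ≈ 0.056, so the shift is about a fifth of one standard error.

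**The case against.** The best defence is that nothing here is wrong. Adjusting for exactly the factors used in the stratification is a recognised, valid primary analysis, and a covariate-adjusted analysis is planned too. Naming its covariates can properly be left to the statistical analysis plan. All of this stands, so the point concerns efficiency only.

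Several stronger readings are tempting, and the article does not support them:

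- **That the trial runs at barely over 80% power.** This is true only at the 22% the article calls conservative. At the observed 24% with RR 0.85 it is about 87%.
- **That two RRs are left with no rule for choosing between them.** The article ties the primary hypothesis to the stratification-only model and labels the other a sensitivity analysis. That settles which governs.
- **That chance imbalance in surgery type threatens the primary estimate.** At this sample size the expected shift is small (step 5).
- **That the cited 10–15% to 61–70% range shows how much surgical category would explain.** Those are one-year figures for mastectomy at one end and thoracotomy and amputation at the other. Mastectomy and thoracic surgery share a single category in this trial, so a four-level covariate cannot capture that contrast.

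Two further objections hold in part. Site and preoperative pain may already absorb some of the surgery effect, which puts the gain towards the low end. The gain is also not entirely free, because more terms make convergence failure likelier in a log-binomial model that may already carry up to 36 site terms.

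**Conclusion.** The point holds as a modest efficiency improvement. It is neither an error nor a contradiction. At the planning rates, a plausible set of baseline covariates would add roughly half a point to two points of power, and about four if they explained 10% of outcome variance.

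This rests on three assumptions: an R² that the article does not supply, the approximation that variance scales with 1 − R², and 6% of patients contributing no information at 3 months although multiple imputation is planned. The case for acting is that the predictors are named in the article, the data are already collected and the change is cheap. It does not depend on the trial being underpowered.

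**What to change.** Before unblinding, specify the primary model as treatment, site, preoperative pain, planned surgical category, age, sex and baseline K-10.

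- Use the four surgical categories of the subgroup section, including the residual one, classified by the operation planned before randomisation and not the one performed.
- Admit no factor that arises after randomisation. Acute postoperative pain, duration of surgery and nerve damage are all listed as risk factors in Background and must stay out.
- Estimate the RR by Poisson regression with robust variance, or by logistic regression standardised to a marginal RR. Either keeps the RR as the summary measure of the estimand and avoids log-binomial convergence failure.
- Keep the stratification-only model as the sensitivity analysis.

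The cost is wording in the analysis plan, a slightly more complex primary model, and imputation of a few missing baseline values. Multiple imputation is already the primary method for missing outcomes, so this adds little.
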